## Abstract

**Background:**

Providing informal care for individuals with dementia is frequently a challenging and demanding experience that can have detrimental effects on the psychological well-being of caregivers. Regrettably, community-based caregiver services often prove inadequate, highlighting the necessity for innovative approaches to support caregivers.

**Aim:**

To test the efficacy of e-bibliotherapy in improving the psychological well-being of informal caregivers of people with dementia.

**Method:**

The study is divided into two phases. In phase 1, the research team will co-design the e-bibliotherapy app with caregivers. In phase 2, a randomized controlled trial will be conducted among 192 informal caregivers of people with dementia in Hong Kong. Caregivers will be randomly assigned to either the e-bibliotherapy group or the control group using simple randomization. Outcome measures will encompass caregivers’ psychological well-being, caregiving appraisal, mental health, saliva cortisol levels as an indicator of stress, and health-related quality of life for caregivers. Data will be collected at baseline, immediately post intervention, and 3 months and 6 months post intervention. General linear mixed model will be employed to analyze intervention effects. Qualitative interviews will be undertaken to explore caregiver experiences within this study and evaluate intervention acceptability using conventional content analysis methods.

**Discussion:**

This study represents a pioneering effort in utilizing e-bibliotherapy to enhance the psychological well-being of informal caregivers of individuals with dementia, addressing the existing gap in caregiver services and facilitating knowledge dissemination within the community.

**Trial registration:**

The trial has been registered on ClinicalTrial.gov (Ref: NCT05927805).

## Background

As the global population ages, the prevalence and burden of dementia are escalating, particularly among older adults [1]. In 2019, over 55.2 million people worldwide were living with dementia, and projections indicate that this number will rise to 78 million by 2030 and 139 million by 2050 [2]. Consequently, this condition necessitates an enhancement of services for people with dementia by governments and healthcare professionals. However, the availability of services remains insufficient to meet the growing demand [3]. As a result, informal caregivers assume a crucial role in providing primary care to individuals with dementia [4].

Approximately 85% of older adults with mild to moderately severe dementia receive care from informal caregivers [5], who are unpaid unprofessional caregivers such as family members [6]. However, caring for a person with dementia can be demanding due to the complex behavioral and psychological symptoms, stigma, and safety risks, which can have detrimental effects on caregivers’ psychological well-being, quality of life, and lead to stress, anxiety, and depression [7–9]. More than 80% of caregivers report high-level stress, and nearly half experience depression during their caregiving role [10]. The poor psychological state of informal caregivers can result in inadequate care and early placement in nursing homes for people with dementia [11]. Our survey of Chinese dementia caregivers revealed that their psychological well-being was unsatisfactory, characterized by low autonomy and low environmental mastery. This was particularly evident during the COVID-19 pandemic, with 72.1% of caregivers experiencing clinical or major depression, in addition to high levels of stress [12]. Another study found that approximately 80% of working dementia caregivers felt depressed or hopeless, and 60.8% reported poor or fair health status [13].

Given the deleterious effects on psychological well-being, informal caregivers have articulated the need for health and social services [14]. The majority of informal caregivers have emphasized their need for assistance with day-to-day care and striking a balance their caregiving role and personal needs [15]. At present, various counselling, emotional support, and respite services are provided for caregivers in Hong Kong [16]. However, the utilization rate of dementia caregiver services remains generally low (< 40%), typifying a global phenomenon [17].

Several factors contribute to this phenomenon. Firstly, the current caregiver services are nonstructured and primarily consist of generic counseling that does not cater to the specific needs of caregivers [16]. Secondly, the limited availability of healthcare professionals results in extensive waiting lists and poor accessibility, with the majority of applicants unable to receive services even after half a year of waiting [16]. Thirdly, caregivers often hesitate to seek help due to their high workload, emotional over-involvement, and a strong sense of filial or social obligation [18]. Our interviews revealed that Chinese dementia caregivers exhibit significant tolerance and reluctance to use services, stemming from their fear of not fulfilling their filial duties [19]. Lastly, and more fundamentally, it is unsustainable to solely rely on external services to address health problems caused by long-term care, and more fundamental changes may be necessary to support informal caregivers.

In light of the current situation, a multitude of studies have been conducted. A published systematic review indicates that psychosocial and psychoeducational interventions tend to be beneficial to dementia caregivers [20]. Among these interventions, cognitive-behavioral techniques have been found to be the most beneficial for enhancing caregiver mental health [21]. Despite the therapeutic benefits demonstrated in previous studies, current services and interventions are predominantly provided in face-to-face or group-based formats, which may not be feasible for those encountering challenges in securing substitute caregivers or those who hesitate to seek help due to stigma [22]. Consequently, there is a pressing need to implement accessible, feasible, convenient, and sustainable interventions that can be integrated into community services. A systematic review revealed that individual self-help interventions could aid in overcoming existing barriers and are more effective than group interventions [23]. It is crucial to provide interventions that can be tailored to the specific needs of caregivers, delivered in a format that is accessible to all caregivers, and sustained over the long term.

Bibliotherapy, an innovative non-pharmacological self-help intervention, has the potential to address the criteria mentioned above. Bibliotherapy is an individual intervention that involves reading materials for therapeutic benefits [19]. Our systematic review indicates that bibliotherapy is effective in improving mental health, with sustained effects [6]. This model of intervention that applies cognitive-behavioral techniques requires few resources and has good sustainability, as caregivers can continue using the reading materials even after the intervention period. The mechanism of bibliotherapy is typically based on the process of the ‘identification-catharsis-insight” process, which guides caregivers to identify their problems, achieve emotional release, and gain insight into cognitive reframing [19].

Our pilot study demonstrated the feasibility and preliminary efficacy of bibliotherapy in enhancing caregivers’ psychological well-being and caregiving appraisal [19]. However, several factors necessitate the need for a full trial. To begin with, participants from the pilot study suggested modifications to the intervention protocol to better cater to caregivers’ needs and enhance usability. The conventional delivery method of written materials restricts dissemination to those with low literacy levels. To overcome this, participants proposed an e-bibliotherapy approach, such as a user-friendly app, to facilitate dissemination to a broader range of caregivers, regardless of their educational background [19]. Our review corroborated the effectiveness of e-bibliotherapy in improving the mental well-being of dementia caregivers [6]. Moreover, although the effect size of caregiving appraisal was moderate, the effect size on psychological well-being was small in the pilot trial. Given that caregiving appraisal is the mechanism driving changes in psychological well-being [12], the small-scale pilot study might have been underpowered to detect a genuine effect on psychological well-being. To validate the effect size observed in the pilot study and establish the generalizability of the findings, a trial with a larger sample size is still required. Furthermore, the pilot study only examined the immediate post-intervention effect, while evidence suggests a sustained effect of bibliotherapy, which has not been extensively studied [6]. Therefore, in this study, we will develop and test an e-bibliotherapy app-based intervention within a fully powered randomized controlled trial. This implementation of this intervention has the potential to facilitate an accessible, convenient, and sustainable approach to enhance the psychological well-being of informal caregivers of people with dementia, ultimately leading to an improvement in the quality of care provided to those with dementia.

## The study

### Aims

To evaluate the efficacy of e-bibliotherapy in improving the psychological well-being of informal caregivers of people with dementia.

### Hypothesis

Participants in the e-bibliotherapy group will demonstrate a greater improvement in psychological well-being than the control group immediately post intervention, and three and six months after completing the intervention.

## Methods

### PHASE I co-design an E-bibliotherapy app

Informed by the feedback obtained from our pilot study and literature review, an e-bibliotherapy app is being developed. The app’s design follows senior-friendly website guidelines, such as font size, contrast, button style and size, menus, and navigation, to ensure usability for caregivers, who are mainly middle-aged and older adults.

To protect the privacy of the participants, each participant will be given a project ID and password to log in to the app. No personal information will be collected while using the app. Only authorized participants and research team members can log in to the app and access the research data. These measures will ensure that the participants’ privacy is protected and that the data collected are secure.

#### App functionalities

The E-bibliotherapy App will include several functions to support the users. The learning functionality will be used to upload the contents of the bibliotherapy manual that was tested in the pilot study. The manual comprises eight chapters, each of which is divided into several sub-sessions. Explanatory mini videos highlighting key information from each session will be produced to enhance participants’ comprehension. Audiobook functionality will be used to allow users to listen to the materials. Mandatory task functionality will be set up to facilitate establishing designated compulsory tasks. Participants will be restricted from advancing to the next session until they have completed the requisite mandatory tasks. Voice input functionality will be used to allow users to complete tasks via auditory input. An e-bulletin will be set up to enable users to read the latest updates and reminders. Finally, a messenger function will allow users to communicate with the researchers. In addition to the above-mentioned functions for users, there will also be a statistical functionality for researchers to monitor the learning progress of each participant and calculate the task completion rate automatically.

#### Co-design the E-bibliotherapy app with end-users

To ensure that the E-bibliotherapy App meets end user’s needs, we will invite them to co-design the app through focus group interviews. The feedback collected from the interviews will be used to maximize the app’s feasibility, usability, and acceptability. Below are the details of the co-design:

##### Sampling

Purposive sampling will be used to recruit a relatively diverse sample in terms of age, gender, educational level, caregiving duration, caregiving intensity, etc. We plan to invite 4 to 8 caregivers in each focus group. Thematic saturation will be used as the criterion for ceasing the interviews.

##### Eligibility criteria for caregivers

To participate in the study, caregivers must meet the following inclusion criteria: (1) be primary caregivers aged 18 or above; (2) provide unpaid regular care to a person with mild or moderately severe dementia consistent with a score between 4 and 6 using the Global Deterioration Scale [24]; (3) have cared for the care recipient for at least six months; (4) assist with at least one of the care recipient’s daily activities; (5) use a smartphone or tablet; and (6) be able to read Chinese.

Caregivers will be excluded if they (1) have unstable physical or mental conditions; (2) have cognitive impairment; (3) are undergoing acute treatment or have not yet stabilized on their chronic medication; and (4) are involved in another interventional study.

##### Data collection

To ensure that participants are familiar with the E-bibliotherapy App prototype, they will be asked to attend a briefing session two days before the focus group. During the briefing, the app prototype will be installed on their smartphones or tablets, allowing them adequate time to acquaint themselves with the app’s features and functionalities.

Each focus group will include a moderator and a note-taker to ensure that all participants’ feedback is captured accurately. Open-ended questions will be asked (e.g., *In general, what do you think of the prototype? What do you think is good about the app? What difficulties or barriers have you encountered when using the app? What recommendations do you have to make the app better fit your needs?*). The interviews will be audio-taped under the participants’ consent. Each interview will last for 60 to 90 min, depending on the natural break. Conventional content analysis will be conducted to capture the feedback from the focus group interviews.

##### E-bibliotherapy app debugging

The app will be adjusted according to the co-design findings and go through pilot testing among 12 caregivers to test the app’s usability [25]. Then, the app will be further debugged based on the pilot study comments.

### PHASE II randomized controlled trial

#### Study design

A single-blinded, parallel-group, two-arm randomized controlled trial. The study protocol complies with the SPIRIT checklist [26] and is registered at ClinicalTrial.gov (Ref: NCT05927805).

#### Setting and sampling

Convenience sampling will be used to recruit participants from government-subsidized community-based elderly service centers. Staff from the centers will recommend potential participants to the research team, and a research assistant will assess the eligibility against the criteria mentioned in the co-design stage. The recruitment process is anticipated to commence in May 2024.

#### Sample size

The sample size was calculated by testing between-and-within interactions in a General Linear Mixed Model (GLMM), using the software “General Linear Mixed Model Power and Sample Size”. Type I and II errors were set at 0.05 and 0.2, respectively. The marginal means of psychological well-being from the pilot study at baseline and post intervention were 84.07 and 86.35, respectively, for the intervention group. For the control group, they were 73.5 and 70.7, respectively. We assume that the follow-up values for the intervention group are equal to 85.7 and 85.2; 71 and 71.3 for the control group. The standard deviation of the pilot study was 13. An autoregressive correlation structure (AR1) with a correlation equal to 0.7 was used. To achieve alpha = 0.05 and power = 0.801, the estimated sample size would be 160. Considering the 20% attrition rate of the pilot study, the estimated sample size would be 192 in total.

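### The printed sample-size inputs give a power of about 0.76 at 160 participants, not the stated 0.801

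*Protocol article*

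**What the plan says.** All of this is in the protocol article, Phase II, under Sample size.

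- **Test:** "The sample size was calculated by testing between-and-within interactions in a General Linear Mixed Model (GLMM"; that is, the group-by-time interaction.
- **Error rates:** "Type I and II errors were set at 0.05 and 0.2, respectively".
- **Pilot means, intervention:** "The marginal means of psychological well-being from the pilot study at baseline and post intervention were 84.07 and 86.35, respectively, for the intervention group".
- **Pilot means, control:** "For the control group, they were 73.5 and 70.7, respectively".
- **Later visits:** "We assume that the follow-up values for the intervention group are equal to 85.7 and 85.2; 71 and 71.3 for the control group".
- **Spread:** "The standard deviation of the pilot study was 13".
- **Correlation:** "An autoregressive correlation structure (AR1) with a correlation equal to 0.7 was used".
- **Result:** "To achieve alpha = 0.05 and power = 0.801, the estimated sample size would be 160".

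**The concern.** An article often leaves the details of a power calculation to a fuller document. This one prints a complete set of inputs and a power to three decimals, so a reader can check the figure, and it does not check.

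The figure is relied on. The Background justifies the trial as an adequately powered successor to a pilot that may have been too small to show an effect on psychological well-being, and the 160 is the base from which the enrolment target is built. If the printed inputs are the ones used, the type II error at 160 is about 0.24 rather than the intended 0.2.

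**Working it through.** **Inputs.** All come from the Sample size section, except equal allocation (80 per arm), which I assume because the article gives no ratio in numbers. An unequal split would lower power.

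| | T0 | T1 | T2 | T3 |
|---|---|---|---|---|
| Intervention mean | 84.07 | 86.35 | 85.7 | 85.2 |
| Control mean | 73.5 | 70.7 | 71 | 71.3 |
| Difference | 10.57 | 15.65 | 14.7 | 13.9 |

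**Step 1. Interaction effect.** Subtracting the baseline difference of 10.57 from each later difference gives θ = (5.08, 4.13, 3.33).

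**Step 2. Covariance of the changes from baseline.** With Σ = 13² × 0.7^|i−j| = 169 × 0.7^|i−j| and U the change-from-baseline contrasts, U′ΣU is 169 times

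| | T1−T0 | T2−T0 | T3−T0 |
|---|---|---|---|
| T1−T0 | 0.600 | 0.510 | 0.447 |
| T2−T0 | 0.510 | 1.020 | 0.867 |
| T3−T0 | 0.447 | 0.867 | 1.314 |

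**Step 3. Noncentrality.** λ = (N/4) × θ′(U′ΣU)⁻¹θ = (160/4) × 0.25577 = 10.23.

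**Step 4. Power at N = 160.** The test has 3 numerator and N − 4 = 156 denominator degrees of freedom, with a 5% critical value of 2.663.

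| Version of the 3-df interaction test | Power |
|---|---|
| Noncentral F(3, 156) | 0.760 |
| Simulation of the same test, 40,000 trials | 0.763 |
| F with between-within df (3, 474) | 0.768 |
| Large-sample chi-square, 3 df | 0.772 |
| Stated in the article | 0.801 |

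The stated figure is not reproduced. The shortfall is 0.801 − 0.760 = 0.041 by the F test and 0.801 − 0.772 = 0.029 by chi-square.

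**Step 5. Number analysed that would give 0.801.** By the F test, power is 0.799 at N = 174, 0.801 at 175 and 0.804 at 176, so about 175 (176 with equal arms). By chi-square it is 171.

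**Step 6. Could rounding of the printed inputs explain it?** The table keeps AR(1) and N = 160.

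| Inputs that would print as the stated ones | Power |
|---|---|
| SD 13, correlation 0.726 | 0.802 |
| SD 12.6, correlation 0.71 | 0.804 |
| SD 12.7, correlation 0.70, pilot means rounded in the favourable direction | 0.8005 |
| SD 12.5, correlation 0.70, means as printed | 0.796 |
| SD 13, correlation 0.70, pilot means rounded in the favourable direction | 0.780 |
| SD 13.49, correlation 0.65 (unfavourable corner) | 0.65 |
| SD 12.5, correlation 0.749 (favourable corner) | 0.87 |

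Favourable rounding of the pilot means takes the intervention values as 84.065 and 86.355 and the control values as 73.55 and 70.65. Rounding the means alone, or the SD alone, does not reach 0.801. An unrounded correlation alone does, and so do modest combinations.

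**The case against.** The strongest reply is that 0.76 is right only if every printed digit is exact. The SD is printed to the nearest whole number and the correlation to one decimal. Across their rounding ranges power runs from about 0.65 to 0.87, and 0.801 lies well inside. That stands, and it limits the point: the printed figures do not show that the calculation was wrong. It does not remove the point, because the article says the correlation was equal to 0.7, and a reader with the printed values obtains 0.76. Rounding could as easily have moved power down.

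A second reply is that a 4-point gap is small beside the uncertainty of the inputs, since the 3- and 6-month means are openly assumed and the pilot was small. This also stands, and it bears on how much weight the point deserves. It does not make inputs and result agree.

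Four stronger readings are tempting and are not supported:

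- **That the calculation used compound symmetry instead of AR(1).** A constant correlation of 0.7 gives 0.814, which is not 0.801 either, and an AR(1) correlation near 0.726 fits more closely. Nothing in the article points to compound symmetry.
- **That true power is nearer 0.6.** Univariate repeated-measures tests do give 0.62 uncorrected and 0.57 with the Geisser-Greenhouse correction, but the article names a mixed model, not those tests.
- **That this error leaves power at about 0.74.** That figure counts only the roughly 153 completers expected from 192 after 20% loss. It mixes in the attrition inflation, which is a separate point, and ignores that a mixed model can use partial follow-up. If all 192 contributed, the printed inputs would give 0.841.
- **That a model constraining the arms to a common baseline mean settles the matter.** It would set aside the printed baseline means, which differ by 10.57 points, so it is not the same calculation. It too is a separate point.

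**Conclusion.** The point holds as an inconsistency between printed inputs and printed result. With the means, SD of 13, AR(1) correlation of 0.7 and 5% level as given, and equal allocation assumed, power at 160 analysed is about 0.76 (0.77 by chi-square). That is about 4 percentage points below the stated 0.801 and below the plan's own 80% target; 0.801 would need about 175 analysed.

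The cause is open. Unprinted digits, or a correlation structure reported differently from the one run, could each account for the gap. A reader might infer that the software run was wrong or that the trial must recruit more caregivers, but the document supports neither conclusion.

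**What to change.** Rerun the calculation from the saved software settings, then do one of two things:

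1. If SD 13, AR(1) 0.7 and the printed means were the exact inputs, restate the power as about 0.76 at 160 analysed.
2. If other values were used, keep 0.801 and print what produced it: the SD and correlation to enough digits, the correlation structure, and the means.

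In either case, name the test statistic and the allocation ratio so that the figure can be reproduced.

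The cost is one rerun and one or two corrected sentences. Under the first option the stated power becomes less favourable. No outcome, analysis or procedure changes, and no extra enrolment is asked for.

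### The 20% attrition allowance was multiplied on (160 × 1.20 = 192) instead of divided out (160 / 0.80 = 200), so 192 covers only 16.7% attrition; the effect on power is small

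*Protocol article*

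**What the plan says.** The Sample size section of the protocol article fixes the error rates ("Type I and II errors were set at 0.05 and 0.2, respectively"), sizes the trial on the group-by-time interaction in a mixed model, and reports the result: "To achieve alpha = 0.05 and power = 0.801, the estimated sample size would be 160". The next step is the attrition allowance: "Considering the 20% attrition rate of the pilot study, the estimated sample size would be 192 in total". The Abstract carries the same number forward: "a randomized controlled trial will be conducted among 192 informal caregivers". No rounding rule and no second attrition rate is given.

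The source of the 20% is the pilot. The Background says of it that "the pilot study only examined the immediate post-intervention effect". The trial itself assesses caregivers at baseline (T0), immediately post intervention (T1), and 3 and 6 months later (T2, T3).

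**The concern.** If 20% of those enrolled are lost, the number left is 0.80 × N. Setting that equal to 160 gives N = 200. Multiplying 160 by 1.20 instead gives an enrolment figure that falls short at the plan's own attrition rate. The design has almost no slack, because power at 160 is 0.801 against a target of 0.80. Any net loss of information below the equivalent of 160 complete records therefore takes the trial under its own target.

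A second, softer point is that the pilot rate covers a shorter period than this trial. It says little about loss between T1 and the 6-month visit.

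**Working it through.** **Inputs (all from the Sample size section).** Required sample size 160; power 0.801; alpha 0.05; attrition 20%; planned total 192. Means at T0, T1, T2 and T3 are 84.07, 86.35, 85.7 and 85.2 for the intervention, and 73.5, 70.7, 71 and 71.3 for control. SD 13; AR(1) correlation 0.7. Equal allocation is my assumption, as no ratio is stated.

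**Step 1: reproduce the plan's figure.** 160 × (1 + 0.20) = 192, an exact match.

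**Step 2: the figure that 20% attrition requires.** 160 / (1 − 0.20) = 200. Check: 200 × 0.80 = 160.

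**Step 3: what 192 delivers.**
- Completers at 20% attrition: 192 × 0.80 = 153.6, so 153 to 154, which is 6 to 7 short of 160.
- Attrition that 192 can absorb: 1 − 160/192 = 16.7%.

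**Step 4: power if dropouts contribute no data.** Take 0.801 at N = 160 as given. For a 3-df F test of the interaction with N − 4 denominator degrees of freedom, that power corresponds to a noncentrality of 11.20. Noncentrality is proportional to N:
- N = 153: 11.20 × 153/160 = 10.71, power 0.781.
- N = 154: 11.20 × 154/160 = 10.78, power 0.784.

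**Step 5: power if a mixed model uses all available records.** The differences between arms in change from baseline are:
- T1: (86.35 − 84.07) − (70.7 − 73.5) = 5.08
- T2: (85.7 − 84.07) − (71 − 73.5) = 4.13
- T3: (85.2 − 84.07) − (71.3 − 73.5) = 3.33

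Each caregiver seen at the first k visits contributes the inverse of the k × k block of 169 × AR(1). These contributions are summed within each arm and inverted to give the covariance of the visit means, and noncentrality follows from the three contrasts above. With 160 complete records the noncentrality is 10.23. All values are multiplied by 11.20/10.23 = 1.095, so that 160 complete records give the stated 0.801. Data are assumed missing at random, and 150 denominator degrees of freedom are used.

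| 192 enrolled, 20% lost by T3 | Scaled noncentrality | Power |
|---|---|---|
| All lost between baseline and T1 | 11.05 | about 0.79 |
| Lost evenly across T1, T2, T3 | 12.65 | about 0.85 |
| All lost after T1 | 13.44 | about 0.87 |

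**Note on the base figure.** Without the scaling, strict AR(1) at 0.7 gives about 0.76 at 160, not 0.801. The software's exact test and correlation settings are not stated, and correlation structures that decay more slowly give 0.79 to 0.81. This is a separate question from the attrition step, so 0.801 at 160 is kept as the article's own base.

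**The case against.** The strongest defence is that the planned analysis is a mixed model over four visits and nothing limits it to completers. Partial follow-up counts, so 153 to 154 completers is not the same as an effective sample of that size. This stands. Step 5 shows that 192 with 20% loss exceeds the information in 160 complete records unless the losses fall mainly before T1, and even then the cost is about one point of power. The defence does not rescue the arithmetic: the sentence still presents 192 as the enrolment for 20% attrition, and it is not.

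It could also be said that 20% was meant as a margin on top of 160. The text calls it the attrition rate of the pilot, so that reading has no support.

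A reader might go further and infer that the shortfall widens at T2 and T3 and erodes power there. The documents do not show this. They give no attrition rate beyond the pilot's, so later head counts would rest on invented rates. The sized test is also driven mainly by T1, where the assumed effect is largest (5.08, against 4.13 and 3.33). If 20% are lost before T1 and a further 10% or 20% of the remainder in each later interval (illustrative assumptions), the Step 5 calculation still gives about 0.79. The pilot's shorter horizon makes 6-month attrition uncertain; it does not make 20% wrong.

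A reader might also recompute power from the stated inputs at 153 and blame the whole gap from 0.801 on the attrition step. Most of that gap is already present at 160 under strict AR(1), so it does not belong to this point.

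**Conclusion.** The allowance is wrong as written: 20% attrition requires 200, and 192 tolerates 16.7%. This part is arithmetic on the article's own figures and needs no assumption.

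The consequence is small. Taking 0.801 at 160 as given, power falls by about two points (to about 0.78) if dropouts contribute nothing, and by about one point (to about 0.79) if their baselines are kept and all losses precede T1. It is above target if losses are spread over the follow-up or come later. These power figures assume equal arms and, for the mixed model, data missing at random.

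The point is a minor correction. It does not support a claim that the trial is materially underpowered, and it changes no hypothesis, test or arm.

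**What to change.** Choose one of the following in the Sample size section:

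- **Keep 192 and restate it.** Say that it allows for 16.7% attrition; or say that 20% attrition leaves about 153 completers, with power about 0.78 on a completers-only basis. This costs one sentence and a slightly less favourable stated power.
- **Correct the target to 160 / 0.80 = 200**, here and in the Abstract. This costs 200 − 192 = 8 more caregivers, about 4% of the planned enrolment.

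In either case, add a clause saying that the 20% was observed in a pilot that ended at the immediate post-intervention assessment, so attrition at 6 months is uncertain.

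### The attrition allowance multiplies 160 by 1.20 instead of dividing by 0.80, so 192 enrolled leaves about 154 completers, not 160, at the plan's own 20% loss (minor)

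*Protocol article*

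**What the plan says.** All the figures are in the protocol article, under Phase II, Sample size.

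- Error rates: "Type I and II errors were set at 0.05 and 0.2, respectively".
- Requirement before attrition: "To achieve alpha = 0.05 and power = 0.801, the estimated sample size would be 160".
- Attrition allowance: "Considering the 20% attrition rate of the pilot study, the estimated sample size would be 192 in total".

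The abstract repeats the enrolled number: "a randomized controlled trial will be conducted among 192 informal caregivers of people with dementia in Hong Kong". The Background describes the intervention as being tested "within a fully powered randomized controlled trial". No other allowance, rounding rule or definition of attrition is given. The efficacy analysis is a mixed model over four assessments (baseline T0, end of intervention T1, and 3 and 6 months later, T2 and T3). The article does not say how caregivers who leave early enter that model.

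**The concern.** An attrition rate is a fraction of the people who start. The number to enrol so that a required number remains is therefore the required number divided by one minus the rate. Multiplying by one plus the rate always gives too few. Here 160, 20% and 192 are all printed, and they do not fit together.

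The planned power at 160 is 0.801 against a target of 0.80, so there is almost no slack. If 160 is the number that must be retained, a shortfall takes the plan below its own target. This holds whether or not 20% is the right rate and whether or not 0.801 at 160 can be reproduced. Both are accepted here.

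**Working it through.** **Inputs.** From the Sample size section: 160 required, 20% attrition, 192 enrolled, alpha 0.05, power 0.801, SD 13, AR(1) correlation 0.7. The intervention means "at baseline and post intervention were 84.07 and 86.35, respectively, for the intervention group", with 85.7 and 85.2 assumed at T2 and T3. "For the control group, they were 73.5 and 70.7, respectively", with 71 and 71.3 assumed at T2 and T3. Allocation is not stated, and 1:1 is assumed.

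**Step 1. Reproduce the plan's figure.** 160 × (1 + 0.20) = 192. It matches exactly.

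**Step 2. Consistent inflation.** 160 / (1 − 0.20) = 200, which is 8 more than 192. Check: 200 × 0.80 = 160.

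**Step 3. What 192 delivers.**
- Completers at 20% loss: 192 × 0.80 = 153.6, about 154.
- Shortfall: 160 − 153.6 = 6.4, and 6.4 / 160 = 4%.
- Loss that 192 can absorb: 1 − 160/192 = 32/192 = 16.7%.

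**Step 4. Power, completers only.** The powered test is the group-by-time interaction over four visits, with 3 numerator degrees of freedom and N − 4 denominator degrees of freedom (noncentral F). To accept the plan's own claim, I solved for the noncentrality that gives 0.801 at N = 160. It is 11.20. Noncentrality is proportional to N:
- N = 153.6: 11.20 × 153.6/160 = 10.76, power 0.782.
- N = 154: 11.20 × 154/160 = 10.78, power 0.784.

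**Step 5. Power, partial records kept.** I took 192 enrolled and 20% lost, with ignorable missingness and known covariance. The differences between arms in change from T0 are 5.08, 4.13 and 3.33 at T1, T2 and T3. They follow from between-arm differences of 10.57 at T0 and 15.65, 14.70 and 13.90 afterwards. For each dropout pattern, the information from all observed visits was summed and turned into an effective N. The noncentrality was then scaled as 11.20 × effective N / 160.

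| When the 20% leave | Effective N (AR(1) 0.7) | Power, with 0.801 at 160 accepted |
|---|---|---|
| Partial records discarded | 153.6 | 0.782 |
| All before T1, baseline kept | 157.8 | 0.794 to 0.797 |
| One third before each of T1, T2, T3 | 180.7 | 0.851 to 0.853 |
| All after T1 | 191.8 | 0.873 to 0.875 |

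The ranges reflect the choice of denominator degrees of freedom. With a constant correlation of 0.7 in place of AR(1), the last three rows become about 0.803, 0.852 and 0.867, so the pattern is not sensitive to that choice.

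**The case against.** The strongest reply is that the planned analysis is a mixed model, which need not discard a caregiver who misses later visits. On that view 154 completers is not the effective sample size. Even a caregiver seen only at baseline sharpens that arm's baseline mean and so adds a little to the interaction. If losses are spread over the visits or come after T1, 192 gives power above 0.801. Even in the least favourable of these patterns the deficit is under one point. This argument stands, and it limits what can be said about power.

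It does not rescue the sentence itself. Inflating 160 for attrition treats dropouts as lost and 160 as the number to retain. If partial records were meant to justify 192, the article would have to say so, and it does not. Early dropout is also plausible: the Background says that the pilot looked only at the immediate post-intervention effect, so its 20% may be loss by T1.

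Two stronger readings are tempting and are not supported:

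- A reader might infer that the trial certainly misses its stated power and is not fully powered. Only the completer count is certain at 20% loss. Power falls below 0.80 only for a completer analysis or, narrowly, if losses come before T1. A 4% shortfall in completers is also small beside the uncertainty in inputs taken from a pilot and in assumed follow-up means.
- A reader who computes power directly from the printed means, SD and AR(1) 0.7 gets 0.740 at 153.6 and might blame attrition for the whole gap from 0.801. The same calculation gives 0.760 at 160, before any attrition. Most of the gap is thus a separate question, which unreported software settings may explain. The attrition arithmetic accounts for only about 0.02.

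**Conclusion.** The error in the count holds and can be checked by hand: 192 is 160 × 1.20, it leaves about 154 completers at 20% attrition, and it covers only 16.7% loss. Nothing elsewhere in the article repairs it.

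The cost in power is at most about 2 points (0.801 to about 0.78), and that applies if only completers count. With partial records kept, power is about 0.795 if every loss precedes T1, and about 0.85 to 0.87 otherwise. These figures assume 1:1 allocation, ignorable missingness, and the plan's own 0.801 at 160.

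The severity is minor: one stated figure needs correcting, and the design, conduct and validity of the comparison are not affected.

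**What to change.** Keep 192 and correct the Sample size section in one of two ways:

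1. State that 192 enrolled leaves about 154 completers at 20% attrition. Restate the power as about 0.78 for completers, or give it conditional on how dropouts enter the mixed model and when they are expected to leave.
2. State that 192 covers a loss of 16.7% before the number falls below 160.

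If the sponsor wants to retain 160 completers at 20% attrition, the consistent enrolment figure is 200, and the abstract must change with it.

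The first two options cost a sentence and need no extra caregivers. Under the first, the stated power becomes slightly less favourable on a completer basis. The third costs 8 more caregivers.
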